### Patient-level intervention approach

Eligible and consenting participants (*n* = 365) will be part of the intervention group and will receive recommendation for the HPV vaccine from providers and clinic staff. Enrolled participants will also complete a self-administered questionnaire at enrollment on a HIPPA compliant online data management database on a tablet device. The survey questions will include sociodemographic characteristics, knowledge of and attitudes towards HPV, HPV vaccination, and anal cancer, and vaccine hesitancy. Participants will be requested to provide consent for their HPV vaccination history to be verified with electronic EMR and GRITS. Participants will then watch a short video on HPV and HPV vaccination that can be viewed on their phones (or the study’s tablet device) while waiting to be seen. Potential participants will be asked to follow the study’s private Facebook page which offers additional educational information tailored towards individuals with HIV on HPV-related disease and general health promotion, and risk reduction tips. The Facebook page will also utilize Facebook Messenger (commonly known as Messenger). The proposed study will utilize Messenger to send reminders for follow up appointments for the next shot in the series and motivational messaging to encourage and promote receipt of the HPV vaccine. Participants will be contacted to complete a post-evaluation survey administered via online, telephone, or a mailed paper copy at 6–9 months after baseline. Participants will receive $25 incentive for completion of baseline and follow up study activities.

### Data analysis plan

#### Study outcomes

Initiation of the HPV vaccine is the primary outcome endpoint (Fig. 2). Initiation of the HPV vaccine is defined as receiving the first or second immunization from the series. This variable will be measured by electronic medical records and GRITS at baseline (historical control) and 24 months post baseline. We hypothesize the initiation rate will be higher than the historical control rate. Completion of the HPV vaccine is the secondary outcome variable. Completion is defined as receiving all three immunizations from the series, regardless of time. This variable will be measured by electronic medical records and GRITS baseline (control) and 24 months post baseline.

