### Clinic selection and patient eligibility

Three HIV community clinics for this study were selected due to agreement to participate in the study, granted study access to electronic medical records, and willingness to make office changes to increase vaccination rates. Patients will be recruited from these three clinics and enrolled in the study based on the following eligibility criteria: 1) HIV positive; 2) 18–45 years of age; 3) understand English; 4) capable of informed consent; 5) have not received or completed the three dose HPV vaccine; 6) no contraindications to receiving the HPV vaccine (i.e., history of an anaphylactic allergy to latex, an immediate hypersensitivity to yeast, current moderate or severe acute illness, and/or are currently pregnant).

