#### Data analyses of primary outcomes

For analysis of the primary (HPV vaccination initiation) and secondary endpoints (HPV vaccination completion), the uptake rate of HPV vaccination pre- and post-intervention will be estimated separately with a 95% exact confidence interval using all eligible cases from both phases. The one-sample binomial exact test will be used to test whether the rate after the intervention is higher than the baseline rate (P0 = 13.5%). We will also perform the Chi-square test to compare the rate change between control and interventional phases, which will be exploratory. Logistic regression will be used to further adjust background difference in study population in pre- and post- intervention phases. For the longitudinal data collected from the intervention phase, the data structure holds multi-level information from patients, providers, and clinic levels. The goal of the analyses is to identify the factors that might impact HPV uptake from each level of information, which might lead to the future improvement of implementation strategy. Data will be described using summary statistics (e.g., quartiles, median, mean, standard deviation) for continuous variables and marginal distribution (frequency and percentage) for categorical variables. The univariate association with the HPV vaccination (yes vs. no) will be tested in logistic regression for each variable separately. The change of survey response between baseline and a follow-up time point will be tested by paired tests (e.g., paired t-test, McNemar test). Along with data visualization, all above mentioned descriptive and univariate association analyses will be repeated within each of the three clinics. Data will be pooled to build the multilevel analysis models, we mainly consider using the mixed-effect model and/or Bayesian multilevel modeling, in which the random effect will be considered at provider and clinical levels. We will follow the key modeling considerations listed by J.J. Hox [29] to identify the significant mediators and moderators at different levels that impact the uptake of HPV vaccination.

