#### Statistical power

Based on our preliminary data, we found that HPV vaccination rate is around 13.5% (P0) in general, and another larger study in the literature found a very similar rate of 13.6% [10]. We powered the study to detect an uptake rate > 13.5% after the intervention. Thus, a sample size of 317 achieves 80% power to detect a superiority difference of 5% (PB-P0) using an exact one-sided test with a significance level (alpha) of 0.05. We anticipate a 5% superiority difference is reasonable to achieve with an uptake rate of 18.5% (PB) after the intervention. We will be able to reject the Null hypothesis and claim the uptake rate of > 13.5% after 54 patients have initiated the HPV test. After taking about 15% of the drop-off rate into account, we plan to include 365 participants among 3 clinics for the intervention phase. The calculation was by PASS 2020 for testing superiority of one proportion using the Exact test. The Null hypothesis is *P* < = 13.5% and the alternative hypothesis is *P* > 13.5%. For the control phase, we will query all eligible subjects from EMR database among the 3 clinics at 18 months pre-intervention, which could be approximately 2300 subjects [30]. Assuming we end up with the same number of subjects in both control (*N* = 317) and intervention phase (*N* = 317), we will have 81% statistical power to detect an HPV uptake rate difference of 9% (22.5% vs. 13.5%) by two-sided Fishers’ Exact Test and under significance level of 0.05. We anticipate such a difference would be feasible based on our best knowledge and the literature. Regarding the patient- level component of the intervention, all incoming eligible patients will be influenced, and hence 365 participants are the minimum number to capture the follow-up information, the actual number of sample size used for the calculation of HPV vaccination rate will be larger as the vaccination status will be captured automatically in EMR without a consent.

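### Criterion 5 can be read to admit patients with one or two earlier HPV doses, and the primary endpoint does not require a first-ever dose dated after baseline, so a continued series may count as an initiation

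*Protocol article*

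**What the plan says.** - **Eligibility** (Clinic selection and patient eligibility, criterion 5): patients must "have not received or completed the three dose HPV vaccine".
- **Primary endpoint** (Study outcomes): "Initiation of the HPV vaccine is defined as receiving the first or second immunization from the series". On timing, the section says: "This variable will be measured by electronic medical records and GRITS at baseline (historical control) and 24 months post baseline".
- **Secondary endpoint** (same section): "Completion is defined as receiving all three immunizations from the series, regardless of time".
- **Dose history** (Patient-level intervention approach): "Participants will be requested to provide consent for their HPV vaccination history to be verified with electronic EMR and GRITS". No rule then uses that history to define the endpoint or the analysis set.
- **Test** (Data analyses of primary outcomes; Statistical power): a one-sided exact binomial test of the post-intervention rate against a fixed 13.5%. It uses N = 317, alpha 0.05 and a planning value given as "uptake rate of 18.5% (PB) after the intervention", and success is claimed at 54 initiators.
- **Analysed patients** (end of Statistical power): the rate will be calculated on more than the 365 enrolled, because vaccination status is available from the medical record without consent.

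**The concern.** The primary claim is that the programme raises the rate at which people living with HIV start the vaccine series. That needs a count of people who had no dose and then received a first one.

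Criterion 5 joins two verbs to one object, the three-dose vaccine. A patient with one or two doses has not completed it and arguably has not received it. The words about completion would also be redundant if any earlier dose excluded a patient.

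The endpoint then names the second dose beside the first. In a wholly dose-naive group this adds nothing, because anyone with a second dose has already had a first. It adds patients to the count only if some enter with a dose already given.

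Taken together, these rules can let a continued series, or a dose that predates the study, count towards 54. The comparator is a fixed number, so nothing on the other side of the test offsets this unless 13.5% was built in the same way.

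**Working it through.** **Inputs.** From Statistical power: P0 = 13.5%, PB = 18.5%, N = 317, rejection at 54, one-sided alpha 0.05. Assumed, because the document gives neither: q, the share of analysed patients with one or two earlier doses, and g, the share of those who count.

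**1. The plan's own rule.** Exact binomial tails at N = 317:
- P(X ≥ 54 | 13.5%) = 0.0425
- P(X ≥ 53 | 13.5%) = 0.0585, which exceeds 0.05

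The threshold of 54 therefore reproduces. Exact power at 18.5% is 0.770 rather than the stated 80%. That is a separate matter and does not affect this point.

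**2. The margin.** Expected initiators under the null are 317 × 0.135 = 42.8. The threshold lies 54 − 42.8 = 11.2 patients above that.

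**3. Every patient with an earlier dose counts** (status read cumulatively, g = 1). Dose-naive patients initiate at 13.5%, so r = q + (1 − q) × 0.135. The chance of a false claim is P(X ≥ 54 | 317, r).

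| q | r | Chance of claiming success |
|---|---|---|
| 0% | 13.5% | 4.2% |
| 1% | 14.4% | 10.3% |
| 2% | 15.2% | 20.5% |
| 3% | 16.1% | 34.7% |
| 5% | 17.8% | 66.6% |
| 10% | 22.2% | 99.0% |

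At q = 5%, 317 × 0.05 = 15.9 patients enter already counted. The threshold then needs 54 − 15.9 = 38.1 new initiators among 317 − 15.9 = 301.1 dose-naive patients. That is 12.7%, which is below the null rate.

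**4. Such patients count only on a further dose in the study.** Now r = q × g + (1 − q) × 0.135.

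| q | g | r | Chance of claiming success |
|---|---|---|---|
| 5% | 0.25 | 14.1% | 7.8% |
| 5% | 0.5 | 15.3% | 21.9% |
| 10% | 0.25 | 14.7% | 13.2% |
| 10% | 0.5 | 17.2% | 54.5% |

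On the literal definition this route covers patients with one earlier dose who receive the second. A patient with two earlier doses who receives the third meets the completion definition, and counts as an initiation only if status is cumulative.

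**5. What both tables assume.** Patients are treated as independent, and 13.5% is taken to contain no earlier doses.

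**The case against.** The case on the other side has real weight.

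- **Criterion 5 has a strict reading.** Under ordinary negation it means neither received nor completed, which excludes anyone with a dose. That would remove the problem for enrolled patients. This stands as a reading, but the text does not settle it.
- **The mention of a second dose may be only a label** for a series begun but not finished, set against completion. This is plausible. It still leaves a definition that does not say the dose must be new.
- **Cumulative status is an inference.** The article gives two measurement times, and Methods/design describes the control as uptake over the 18 months before the intervention, which can be read as a window. Dating rules may sit in the full protocol or the SAP. This stands against the g = 1 table, but less against the second route, where the dose falls inside the study.
- **13.5% may be an ever-vaccinated rate.** Statistical power describes it only as a general vaccination rate from preliminary data. Earlier doses would then be partly in the null already, and the inflation would be smaller than either table shows. This stands. The endpoint would then still not isolate new initiation.
- **A second dose in the study may be the programme's doing,** since reminders for the next dose are part of it. This stands: such a dose is not inflation without effect. It is continuation counted under the name of initiation.

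A reader might infer that already-vaccinated patients will be enrolled and counted as successes from entry, so that the true error rate is 66.6% or 99.0%. The documents do not support that. Criterion 5 is ambiguous, cumulative counting is not stated, and q is nowhere given.

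**Conclusion.** The point holds in a limited form. The article states an endpoint rule that does not require a first-ever dose after baseline, beside an eligibility rule that does not clearly exclude earlier doses. This is more than detail left to another document: the stated wording, taken literally, allows a series continuation to count as an initiation in the primary test.

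The size is conditional. If dose-naive patients initiate at 13.5%, the chance of claiming success rises from 4.2% to 20.5% (q = 2%) or 66.6% (q = 5%) when all patients with earlier doses count. When half of them count through a further dose in the study, it is 21.9% (q = 5%) or 54.5% (q = 10%). If criterion 5 is applied strictly to everyone analysed, the problem disappears. If 13.5% is an ever-vaccinated rate, it shrinks by an amount that cannot be computed from the article. The margin of about 11 patients is narrow enough to justify settling the wording before the primary analysis.

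**What to change.** 1. Reconcile criterion 5 with the endpoint definition, so that the text says plainly whether patients with one or two earlier doses may enter.
2. Restrict the primary analysis set to patients with no HPV dose recorded in the EMR or GRITS at the start of the window.
3. Define initiation as a first dose dated within the window, and state that patients who go on to complete the series are included.
4. Apply the same rule to the historical cohort, and state or re-derive P0 = 13.5% on that definition. Without this step the numerator and the null would measure different things.
5. If partly vaccinated patients are enrolled, analyse them for completion only, as a separate stratum.

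**Cost.** Both record systems are already to be queried, so this is mainly a change of wording. The primary denominator becomes smaller, by an amount that depends on the unknown q, and both P0 and the 54-patient threshold must be rechecked. The history check at enrolment covers consenting participants only. For the larger group analysed without consent, the sponsor should confirm that dose dates can be obtained from the same sources.

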**Fig. 2 Fig2:**
[figure not shown]
Summary of study assessments and time of collection

#### Process evaluation

The RE-AIM (Reach, Effectiveness/Efficacy, Adoption, Implementation, Maintenance) framework will guide planning, implementation, and evaluation of the 4 Pillars™ program. The study’s reach will be estimated from a quantitative perspective by estimating the target population that was exposed to the intervention. The clinic’s patient census data during the period of the implementation phase will be used to estimate the likely reach of the program across sites. Intervention effectiveness and efficacy will be measured by the change in uptake rate of vaccination (i.e., intervention effectiveness). We will calculate the percent change in initiation of the vaccine and percent change in completion of the vaccine from the control phase and 24 months post intervention, after adjusting for demographics differences (age, gender, race, healthcare insurance) in population. Providers and clinic staff will be asked to complete an evaluation of HPV vaccination progress every 3-months. We will also collect qualitative data from feedback sessions with the immunization champions to assess opportunities for and barriers to adoption. The post-evaluation interviews with providers and staff who implemented the program will assess extent of involvement, acceptance of the intervention, implementation fidelity, and extent of organizational spread of the intervention. We will assess the frequency, duration, and the extent to which the intervention was implemented as planned, participation attendance, and costs of implementation, as measured via the intervention and post-intervention evaluations. Intervention sustainability will be measured as the gains or maintenance of HPV vaccination rates post-delivery of the intervention. HPV vaccination rates will be calculated via EMR and GRITS at month 36 (12 months post intervention) and compare to HPV vaccination rates at month 24. Follow up assessments will measure penetration or the extent to which recommendation and administration of the HPV vaccination is integrated within the clinic.

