#### Secondary aims

To assess sustainability, HPV vaccination rates will be calculated at month 36 (12 months post-intervention). The change in HPV vaccination rates between month 24 and month 36 (12 months post-intervention) will be tested by McNemar test. The intervention will be deemed as sustaining its effect if rates of HPV vaccine initiation rates at month 36 remains or increases from month 24’s vaccination rates. To inform future scalability of the program, data from the evaluation and post-evaluation surveys will be described using summary statistics (e.g., quartiles, median, mean, standard deviation) for continuous variables and marginal distribution (frequency and percentage) for categorical variables. The similar analyses will be repeated within each of the three clinics. Additionally, we will conduct a post-intervention focus group consisting of the providers and clinic staff that participated in the program. The qualitative evaluation explore how implementation took place; the barriers to and facilitators of implementation success; ways to address any problems that may have occurred; and recommendations to refine the intervention for scale-up. The focus session will be recorded and transcribed where themes will be extracted and used for adaptation, scale-up considerations, and future research directions.

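### The readout time of the primary and secondary endpoints is stated in ways that do not agree, and no single patient-level clock or equal window is fixed for the two phases

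*Protocol article*

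**What the plan says.** All places are in the Protocol article.

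- Study outcomes, on initiation: "This variable will be measured by electronic medical records and GRITS at baseline (historical control) and 24 months post baseline". Completion gets the same two time points, and "Completion is defined as receiving all three immunizations from the series, regardless of time".
- Process evaluation, on effectiveness, gives the change in initiation and the "percent change in completion of the vaccine from the control phase and 24 months post intervention".
- Process evaluation, on sustainability: "HPV vaccination rates will be calculated via EMR and GRITS at month 36 (12 months post intervention"), to be compared with the rates at month 24. Secondary aims repeats this: "The change in HPV vaccination rates between month 24 and month 36 (12 months post-intervention) will be tested by McNemar test".
- Patient-level intervention approach uses baseline for the participant's own entry to the study. The follow-up survey is "administered via online, telephone, or a mailed paper copy at 6–9 months after baseline".
- Methods/design sets the control look-back at 18 months before the intervention.
- Statistical power says that the rate will also include patients whose vaccination status is taken from the medical record without consent. These patients have no enrolment date.

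The text gives no enrolment period and no minimum length for the vaccine series. It does not say whether month 24 is one date for all or each participant's own month 24.

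**The concern.** The primary and secondary endpoints are cumulative proportions, so their values depend on how long each patient is observed. If the start and end of observation are ambiguous, two analysts following the article could extract different data and report different rates.

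Two opposite distortions are possible. A common calendar date would give patients who enter late less time to start the vaccine, and less again to finish a three-dose series that is otherwise counted without a time limit. A full 24 months for everyone would set a 24-month rate against a control observed for 18 months. The first works against the programme and the second works for it. The article does not say which applies.

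**Working it through.** **1. The stated times side by side (no assumption needed).**

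- Study outcomes: baseline + 24 months, with baseline glossed as the historical control.
- Process evaluation and Secondary aims: month 36 is 12 months after the intervention, so the intervention ends at month 36 − 12 = 24.
- Process evaluation, effectiveness: 24 months after the intervention. Counted from its end, this is month 24 + 24 = 48, which is 48 − 36 = 12 months after the last assessment named in the text.
- The three agree only if the effectiveness sentence means 24 months after the intervention starts and baseline means the study start date. The second condition does not fit the use of baseline for a participant's own enrolment.

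**2. Who would be short of time at a common month 24.** The assumptions, not in the article, are uniform enrolment over E months from programme start and at least L months needed to finish a series. Share with less than L months = max(0, E − (24 − L)) / E.

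- E ≤ 12: 0% for any L up to 12.
- E = 18: L = 6 gives 0/18 = 0%; L = 9 gives 3/18 = 17%; L = 12 gives 6/18 = 33%.
- E = 24: L = 6 gives 6/24 = 25%; L = 9 gives 9/24 = 38%; L = 12 gives 12/24 = 50%.
- If each participant has 24 months from enrolment: 0% throughout.

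**3. Sensitivity of the observed rates at a common month 24.** Further assumptions: 18.5% (the target rate in Statistical power) is reached at 24 months at a constant rate, so λ = −ln(1 − 0.185)/24 = 0.00852 per month. Every initiator finishes, and a series takes at least 6 months.

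- Mean initiation = 1 − 0.815 × (e^(λE) − 1)/(λE). For E = 12, 18, 24 this is 14.2%, 11.9%, 9.6%, with mean follow-up 24 − E/2 = 18, 15, 12 months.
- Mean completion averages 1 − e^(−λ(18 − u)) over entry times u, with zero for u > 18. This gives 9.7%, 7.3%, 5.5%, against 1 − e^(−18λ) = 14.2% when all have 24 months.
- Probability of reaching the stated 54 of 317 (exact binomial): 77% at 18.5%, and about 9% at the 14.2% seen with E = 12. The article states 80% power for this test. That gap is a separate matter and does not depend on the clock.

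**4. The opposite distortion.** Suppose that 13.5% is an 18-month rate (the article does not say so) and that the rate is constant. Then λ = −ln(1 − 0.135)/18 = 0.00806, and over 24 months 1 − e^(−24λ) = 17.6% with no programme effect. The chance of reaching 54 of 317 is then about 62%, against 4.2% at a true 13.5%.

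Steps 3 and 4 show that the window can matter in either direction. They do not estimate what will happen in this trial.

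**The case against.** The strongest reply is that this is loose wording. Methods/design and Statistical power count the 18 months back from the intervention as if its start were time zero. Counted forward in the same way, 24 months after the intervention is programme month 24, which fits the sustainability text, and no month-48 assessment appears anywhere. Figures 1 and 2, the second of which summarises collection times, are not shown, and a condensed article need not give the accrual period. This makes the intended meaning easy to guess. It does not make the sentences agree, because within Process evaluation the same phrase is counted from the end of the intervention for month 36.

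A reader might infer that late enrolees will have too little time and that completion will therefore be understated. The documents do not support this as a fact. It needs both a common calendar date and late enrolment, and neither is stated. If each participant has 24 months, or if enrolment closes within 12 months and a series takes no more than 12, nobody lacks time to finish a series. Patients who "have not received or completed the three dose HPV vaccine" appear to include some already part-way through, who need fewer doses. The constant-rate assumption is also unfavourable: education and vaccine recommendation take place around clinic visits, so initiation may be concentrated near enrolment. Against the fixed 13.5%, any shortfall would be conservative.

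A reader might also infer that third doses given in months 24 to 36 make the effect look sustained. The stated criterion under Secondary aims concerns initiation, which a third dose does not change. Only a comparison of completion between the two months would be affected.

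The common-date reading remains a serious possibility, because month 36 is tied to the end of programme delivery and the patients counted without consent have no enrolment date.

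**Conclusion.** The inconsistency stands on the text alone: the readout time is given in three forms that do not agree, the literal Process evaluation time is month 48, and baseline has two meanings.

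The effect on the results is conditional and its direction is not fixed. With a common month 24 and late enrolment, initiation and completion may be understated. Under the stated assumptions initiation falls from 18.5% to between 14.2% and 9.6%, and completion from 14.2% to between 9.7% and 5.5%. With 24 months for every patient there is no such loss, but the post-intervention window is 24 − 18 = 6 months longer than the control look-back, which would favour the intervention. These figures are sensitivity results under assumed accrual, series length and a constant rate.

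The point is worth correcting before data extraction, since it fixes when the primary and secondary endpoints are read.

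**What to change.** - Correct the effectiveness sentence in Process evaluation so that it agrees with Study outcomes and Secondary aims. Use separate terms for the control phase and for a participant's enrolment.
- Define one clock from each patient's index date: enrolment for consented participants, and the first eligible visit in the window for patients counted from the record without consent. Apply the first-eligible-visit rule in the control phase too.
- Use the same fixed window length in both phases, and state the period to which the 13.5% reference refers.
- Choose a window W that the last enrolee can complete by the planned month-36 extraction. If enrolment runs E months from programme start, W ≤ 36 − E: 24 months for E = 12, 18 for E = 18, 12 for E = 24.
- In any month-24 versus month-36 comparison of completion, report third doses of series begun before month 24 separately.

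The cost is protocol wording and a date calculation on record and registry data already planned. The final completion figure may come later, or the window may be shorter than 24 months. A window longer than 18 months means extending the control look-back. Where a patient's window runs past month 24 it includes time after programme delivery, and the report should say so.

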## Methods/design

A pre-post intervention study design is used where HPV vaccination initiation and completion rates are measured before and after the intervention across the same clinics and enrolled participants (Fig. 1). HPV vaccination uptake 18 months before intervention will be queried from electronic medical records (EMR) and Georgia Registry of Immunization Transactions and Services (GRITS), which will serve as the historical control. GRITS is a population-based web application containing consolidated demographic and immunization history information. The use of a concurrent control is to reassess the background HPV uptake rate among PLWH during an adjacent time-period to post-intervention and similar population resources. The comparison of HPV vaccination rates pre- and post-intervention in the three selected representative HIV clinics in Georgia will be an exploratory goal of the trial due to the retrospective approach in the control phase and the prospective approach in the post intervention phase. A “within” analysis will be conducted to compare sites both pre- and post-intervention.

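### The covariates listed for the adjusted pre-post change omit clinic, so the pooled estimate can absorb a shift in clinic mix between phases

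*Protocol article*

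**What the plan says.** **Adjusted change.** *Process evaluation* takes the percent change in initiation and completion between the control phase and 24 months as the effectiveness measure, "after adjusting for demographics differences (age, gender, race, healthcare insurance) in population". Clinic is not among the four variables.

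**Pre-post model.** *Data analyses of primary outcomes* states: "Logistic regression will be used to further adjust background difference in study population in pre- and post- intervention phases". It names no covariates.

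**Status.** *Methods/design* says that the pre-post comparison "will be an exploratory goal of the trial due to the retrospective approach in the control phase" and the prospective approach afterwards. The chi-square comparison of phases is also called exploratory.

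**Where clinic does appear.**
- *Methods/design* plans a 'within' analysis: "analysis will be conducted to compare sites both pre- and post-intervention". No model is given.
- *Data analyses of primary outcomes* says that "all above mentioned descriptive and univariate association analyses will be repeated within each of the three clinics". These repeats are unadjusted.
- The same section says that "the random effect will be considered at provider and clinical levels", but the passage leading to that model opens with "For the longitudinal data collected from the intervention phase, the data structure holds multi-level information". Its stated purpose is to find factors, mediators and moderators of uptake.

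**Who is compared.** *Statistical power* takes all eligible patients in the records of the three clinics as the control phase, "which could be approximately 2300 subjects". It plans 365 participants over the three clinics for the intervention phase and states no share per clinic.

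**The concern.** The two phases are drawn from the same three clinics but not necessarily in the same proportions. The control phase is a records query. The enrolled intervention group depends on consent, and recruitment need not follow clinic size. Much of the intervention is delivered clinic by clinic (in-service training, one Immunization Champion per site, vaccine stock), so clinic is a plausible determinant of uptake.

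If a clinic with higher background uptake contributes a larger share after the intervention than before, the pooled rate rises although no clinic has changed. If its share is smaller, a real gain is masked. Age, gender, race and insurance remove this only as far as they explain the clinic difference.

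What is at stake is the adjusted change that the article uses as its RE-AIM effectiveness measure, not the primary test.

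**Working it through.** **Inputs from the article.** Control phase about 2300; intervention phase 317 evaluable (365 planned); reference rate 13.5%; pre-post design alternative 22.5% against 13.5% with 317 per phase, two-sided 0.05; primary design difference 5 points.

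**Inputs assumed.** Clinic rates and clinic shares, because the article gives neither. All scenarios have no intervention effect in any clinic.

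**Step 1: the plan's own figure for this comparison.** Full enumeration of the two-sided Fisher exact test over Binomial(317, 0.135) and Binomial(317, 0.225) gives power 81.8%. The article states 81%, so the figure reproduces.

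**Step 2: spurious change from clinic mix.** The pooled rate is the sum over clinics of share × clinic rate. With rates 8.5%, 13.5% and 18.5%:
- Before, equal shares: (8.5 + 13.5 + 18.5)/3 = 13.5%.
- After, 20/30/50: 0.20×8.5 + 0.30×13.5 + 0.50×18.5 = 1.70 + 4.05 + 9.25 = 15.0%, a change of +1.5 points. Odds ratio (0.150/0.850)/(0.135/0.865) = 1.13.
- After, 10/20/70: 0.10×8.5 + 0.20×13.5 + 0.70×18.5 = 0.85 + 2.70 + 12.95 = 16.5%, a change of +3.0 points. Odds ratio (0.165/0.835)/(0.135/0.865) = 1.27.

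Reversing the shares reverses the sign: 50/30/20 gives 4.25 + 4.05 + 3.70 = 12.0%, a change of −1.5 points.

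**Step 3: other spreads between clinics.**

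| Assumed clinic rates (%) | Mix 20/30/50 | Mix 10/30/60 |
|---|---|---|
| 11.5 / 13.5 / 15.5 | +0.6 points (OR 1.05) | +1.0 (OR 1.09) |
| 8.5 / 13.5 / 18.5 | +1.5 (OR 1.13) | +2.5 (OR 1.22) |
| 5 / 13.5 / 22 | +2.55 (OR 1.22) | +4.25 (OR 1.38) |

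With equal shares in both phases, or equal clinic rates, every entry is zero.

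**Step 4: effect on the test of this contrast.** Take the planned chi-square test at two-sided 0.05, without continuity correction, with 2300 control patients at 13.5% and 317 intervention patients. It rejects 5.0% of the time with no shift, 12% at 15.0% and 31% at 16.5%. This test is unadjusted. For the adjusted model these are upper figures for each scenario, to the extent that the four listed covariates explain part of the clinic difference.

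**Step 5: with clinic in the model.** The comparison is then made within clinics, so the phase odds ratio is 1.00 in every scenario above, by construction.

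**The case against.** **All eligible cases may be used in both phases.** *Data analyses of primary outcomes* says that the rates use all eligible cases from both phases. *Statistical power* adds that the number behind the vaccination rate will exceed 365, because the medical record captures status without consent. On that reading, a census of three clinics is compared with a later census of the same clinics, and no consent-driven shift follows. This stands in large part. The shift shrinks, though it need not vanish because clinic caseloads can change. The wider shifts shown apply mainly if the 365 enrolled participants are the group analysed.

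**Clinic differences are not shown.** A reader might infer that the clinics do differ in uptake and that the mix will differ. The article supports neither as fact. It gives no clinic-level rate and no share, and both conditions are needed for any bias.

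**The covariate list may be open.** The list in *Process evaluation* describes demographic differences. The regression in *Data analyses of primary outcomes* refers only to background difference and names no covariates, so the exclusion of clinic there is inferred. Full model specification may also sit in an analysis plan that is not shown. This stands as a caution, but the one list the article does state leaves clinic out.

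**Clinic is handled elsewhere.** The within-site analysis and within-clinic repeats are free of clinic-mix bias and could expose it. They do not correct the pooled adjusted change, and the random effects are introduced for intervention-phase data.

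**The comparison is exploratory.** This is correct, and it limits the consequence.

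**Conclusion.** The point holds in a limited form. The only covariate list stated for the adjusted pre-post change omits clinic, and nothing in the article places clinic in the pooled pre-post regression. The adjusted change can therefore absorb a clinic-mix shift in either direction.

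Over the assumed scenarios the spurious change runs from 0 to about 4 points, against design differences of 5 points (primary test) and 9 points (pre-post). It rests on three assumptions: clinic rates differ, shares change between phases, and the listed covariates do not explain the clinic difference. The first two cannot be checked from the article.

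A stronger inference would be that this omission undermines the primary result. With the same assumed mixes, the chance of reaching 54 of 317 with no effect is 17.4% at a pooled 15.0% and 42.2% at 16.5%, against 4.2% at 13.5%. Those figures belong to the one-sample exact test against a fixed 13.5%, which uses no covariates and no control-phase data. They do not measure the fault in the adjusted contrast, and adding clinic to the regression leaves them unchanged. The finding concerns an exploratory analysis and is worth correcting because the correction is nearly free.

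**What to change.** - Add clinic as a fixed effect (two parameters for three clinics) to the exploratory pre-post logistic regression, and add it to the covariates named in *Process evaluation* for the adjusted change.
- Report that estimate beside the planned within-site results, and give the 'within' analysis a defined form by using the clinic-by-phase term.
- Tabulate the number of patients per clinic in each phase, so that the reader can see whether the mix moved.

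The cost is a few words in the analysis plan and two model parameters. Clinic should be known for every patient, since both phases draw on the records of the three clinics, so no new data are needed. The change leaves the primary one-sample test as it is.
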